#### Internal pilot summary

The pilot will be conducted over an interval of 6 months, including secondary and tertiary referral centres. The internal pilot aims to determine the number of eligible and recruited patients in the centres over the course of 6 months. If recruitment targets are not achieved a review of the reasons will be investigated in terms of ineligibility due to protocol eligibility requirements, poor site performance and lack of suitable patient population. If targets are met, and any issues resolved, the trial will proceed into the main phase, including patients from the internal pilot. If the trial does not progress to Phase 2, those participants already enrolled in Phase 1 will be followed up as per protocol.

All adult patients presenting at trial centres requiring surgery via a midline laparotomy incision as the primary operative access are eligible for inclusion. Patients will be excluded if pregnant, if they have undergone a relook laparotomy, if their abdomen is left open or if unable to adhere. Randomization will be stratified by trial centre, emergency or elective procedure, and surgical specialty (upper gastrointestinal, lower gastrointestinal, general, vascular, urology). Randomization will be generated and administered via a secure web service, Sealed Envelope, using minimization. The random allocation will be to either standard wound dressing or single-use NPWT. Participating patients will have clinical follow-up for 6 months. Wound photographs will be taken at 1-month, 3-month and 6-month visits. The photograph at 1 month will assist with diagnosis of any infection. Photographs from the 1-month, 3-month and 6-month visits will be used by the clinician to evaluate wound healing together with a patient-reported assessment using the patient and observer scar assessment scale (POSAS) questionnaire^25^. EuroQol 5-Dimension 5-level (EQ5D-5L) quality of life questionnaires will be completed before surgery and at 1 month, 3 months and 6 months to collect quality of life outcome data^26^. At 3 and 6 months, the patient will complete a Cost for Patients Questionnaire (CoPaQ) to evaluate the financial impact on the patient^27^. Information regarding resource use, late complications or additional interventions related to their index procedure will be used to evaluate the financial impact on the healthcare system. Patient monitoring will be performed by the clinical teams responsible for the management of these patients after surgery.

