### Study objectives

The primary objective for the trial is to quantify and analyse differences in the rates of midline wound SSI in the 30 and 90 days following laparotomy between NPWT and standard dressings. The diagnosis of SSI will be made using Centre for Disease Control criteria.

The secondary objectives are to analyse health-related quality of life in the 6 months following laparotomy and to assess the quality of wound healing and cost effectiveness. Another objective is to analyse the further interventions related to laparotomy and the risk of developing SSI related to the subcutaneous adiposity and lean muscle mass using preoperative computed tomography (CT). In a nested Study Within A Trial (SWAT), another objective is to determine the impact of digital prompts (for example using e-mail) to research team members on site trial recruitment rates.

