### Statistical analysis

Standard statistical summaries and graphical plots will be presented for the primary outcome measure and all secondary outcome measures. Baseline data will be summarized to check comparability between treatment arms.

The main analysis will investigate differences in the primary outcome measure: the proportion of patients with any SSI at 30 and 90 days postlaparotomy. While clustering effects are not expected to be important for this study, in reality the data will be hierarchical, with patients naturally clustered into groups by recruiting centre. This will be accounted for by generalizing the conventional linear (fixed-effects) regression approach to a mixed-effects logistic regression analysis. This model will be used to assess differences in SSI rates between the study intervention groups, with results presented as odds ratios with associated 95% confidence intervals. The mixed-effects model will include a random effect to account for any heterogeneity in response due to the recruitment centre and fixed effects to adjust for emergency *versus* elective procedure and surgical specialty. An identically structured and formulated mixed-effects linear regression model will be used to assess the effects of the interventions on secondary outcomes and EQ-5D and WoundQoL (at both 3 and 6 months) that, for the purposes of analysis, will be assumed to be approximately normally distributed. Other dichotomous outcome variables, such as complications related to the trial interventions, will be analysed in the same manner as the primary outcome. Temporal patterns of any complications will be presented graphically and if appropriate a time-to-event analysis (Kaplan–Meier survival analysis) will be used to assess the overall risk and risk within individual classes of complications.

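### The stated EQ-5D model leaves out the preoperative EQ-5D score and, on its most natural reading, gives no treatment contrast at month 1, although both scores are collected

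*Protocol article*

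**What the plan says.** **Collection.** The Internal pilot summary of the protocol article schedules the EQ-5D-5L four times: "quality of life questionnaires will be completed before surgery and at 1 month, 3 months and 6 months".

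**Model.** The Statistical analysis section first sets out a mixed-effects logistic model for SSI. Besides treatment, its only covariates are the urgency of the operation and the surgical specialty, both as fixed terms. Its only random term is described as "a random effect to account for any heterogeneity in response due to the recruitment centre". The same section then carries that structure over to the continuous outcomes: "An identically structured and formulated mixed-effects linear regression model will be used to assess the effects of the interventions on secondary outcomes". The outcomes and visits are given as "secondary outcomes and EQ-5D and WoundQoL (at both 3 and 6 months", followed by a closing bracket.

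**Objective and other uses.** Study objectives states: "The secondary objectives are to analyse health-related quality of life in the 6 months following laparotomy". Secondary outcome measures adds QALY profiles based on the EQ-5D-5L. Statistical analysis also promises descriptive summaries and plots for every secondary outcome.

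**The concern.** A model built for SSI has no baseline value of its outcome to adjust for, because nobody has an SSI before surgery. EQ-5D does have a baseline value, and the trial collects it. Copying the SSI structure unchanged leaves out the covariate likely to be among the strongest predictors of a patient's later EQ-5D. The variation it would explain stays in the residual and widens the confidence interval for the treatment difference.

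The second part concerns visits. If the bracket applies to EQ-5D, the model gives contrasts at 3 and 6 months and none at month 1. That sits badly with an objective covering the whole 6 months, and with a primary outcome first counted at 30 days.

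The trial is powered for SSI alone, and no EQ-5D standard deviation or detectable difference is given. Precision that costs no patients is therefore worth having for this outcome.

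**Working it through.** **1. Schedule against model.**

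| EQ-5D-5L assessment | Collected | Role in the stated model |
|---|---|---|
| Before surgery | yes | none; not a covariate |
| 1 month | yes | none, if the bracket covers EQ-5D |
| 3 months | yes | outcome |
| 6 months | yes | outcome |

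**2. Number analysed per arm.** The article gives no EQ-5D sample size, so the SSI calculation supplies n. The inputs from Power calculation are 15% against 10% and 90% power at the 5% level. Statistical analysis makes tests two-sided, and Randomization sets a 1:1 ratio. With unpooled variances:

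n = (0.15 × 0.85 + 0.10 × 0.90) × (1.960 + 1.282)² / 0.05² = 914.1, so 915 per arm.

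Adding 10% and doubling gives 2 × 915 × 1.10 = 2013, the article's total. I therefore take 915 per arm as the number analysed.

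**3. Gain from the baseline score.** Let r be the correlation between preoperative and follow-up EQ-5D that remains after centre, urgency and specialty. The document does not give r, so a range of 0.3 to 0.6 is assumed. The formulas, in residual standard deviations (SD) of the model without the baseline score, are:

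- variance factor = 1 − r²
- standard-error factor = √(1 − r²)
- equivalent n per arm = 915 / (1 − r²)
- difference detectable with 90% power = (1.960 + 1.282) × √(2/915) × √(1 − r²)

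Without the baseline score, the detectable difference is 0.152 SD, and power for an illustrative true difference of 0.12 SD is 73%. With it:

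| Assumed r | Variance factor | Fall in standard error | Equivalent n per arm | Detectable difference (SD) | Power at 0.12 SD |
|---|---|---|---|---|---|
| 0.3 | 0.91 | 5% | 1005 | 0.145 | 77% |
| 0.4 | 0.84 | 8% | 1089 | 0.139 | 80% |
| 0.5 | 0.75 | 13% | 1220 | 0.131 | 84% |
| 0.6 | 0.64 | 20% | 1430 | 0.121 | 89% |

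The residual variance falls by 9% to 36%. That is the precision of 1/0.91 = 1.10 to 1/0.64 = 1.56 times as many patients.

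**4. Month 1.** No arithmetic applies. The bracket follows a list ending in EQ-5D and WoundQoL. Its most natural reading covers both, which leaves EQ-5D without a modelled contrast at month 1. If it covers WoundQoL alone, EQ-5D has no stated visit at all. The text needs settling either way. The baseline omission does not depend on the bracket.

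**The case against.** **Detail belongs in the SAP.** The article says a detailed SAP will be agreed, and what an article leaves to it is not missing. This defence covers the form of a repeated-measures analysis and any QALY model, which the article does not state. It does not cover the baseline score, because the article itself fixes the covariates of the EQ-5D model by tying it to the SSI model.

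**There is no bias.** This stands. Randomization keeps the unadjusted comparison valid. With 915 per arm, a chance difference in mean preoperative score would mostly lie within 1.96 × √(2/915) = 0.09 SD.

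**The gain may be small.** This stands in part. The relevant r is what remains after the existing covariates, which may already explain some of both scores. It may be lower in emergency patients, whose preoperative score can reflect acute illness. At r = 0.3 the standard error falls by only 5%.

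**Stronger readings that a reader might infer.** The documents do not support these:

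- *Month-1 scores are unused or never examined.* They can still enter the descriptive summaries and the QALY profiles. What is absent, on the natural reading, is a modelled contrast.
- *The quality-of-life effect is largest at month 1.* No section says so. The primary outcome is "the proportion of patients with any SSI at 30 and 90 days postlaparotomy", so the 3-month visit matches its second time point.
- *Baseline imbalance will distort the QALY comparison.* The article states no QALY model, so it cannot be faulted for leaving QALYs unadjusted.
- *A single repeated-measures model is required.* Separate models at each visit are also valid.

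**Conclusion.** The point holds in limited form. The stated EQ-5D model omits a preoperative score that the trial collects, and the comparison remains unbiased without it. The cost is precision on a secondary outcome: about 9% to 36% of the residual variance, or about 5% to 20% of the standard error. These figures rest on an assumed residual correlation of 0.3 to 0.6; the true loss cannot be derived from the document. The detectable differences and power also rest on 915 analysed per arm, and the 0.12 SD difference is only illustrative.

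On visits, the conclusion is narrower. The most natural reading gives no modelled contrast at month 1, which fits poorly with a 6-month objective and a 1-month assessment. The wording is ambiguous enough that it should be clarified, not treated as a settled decision to ignore month 1.

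**What to change.** 1. Add the preoperative EQ-5D score as a fixed-effect covariate in the EQ-5D model, alongside urgency, specialty and the random centre effect.
2. Prespecify how randomized patients with a missing preoperative score stay in the analysis. The multiple imputation already foreseen in Statistical analysis is one route; mean imputation with a missing-value indicator is another. Either works if chosen in advance.
3. If QALYs are compared between arms, use the same baseline adjustment there.
4. State that EQ-5D is compared between arms at 1, 3 and 6 months, in separate models per visit or in one repeated-measures model. The latter needs a patient-level term, because the random effect now stated is for centre only.
5. While editing that sentence, say which instruments the bracketed visits apply to. WoundQoL appears there but not in the collection schedule or under Secondary outcome measures.

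The cost is a change of wording in the protocol and SAP, one more secondary comparison and slightly more analysis. No new data, visits or patients are needed. The change should be made before any comparison by arm is seen, so that the adjustment is prespecified.

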**Methods:**

PROPEL-2 is a multicentre prospective randomized clinical trial designed to compare standard surgical dressings (control arm) with negative pressure wound therapy dressings (Prevena™ and PICO™ being the most commonly utilized). Patient recruitment will include adult patients aged 18 years or over, who are indicated to undergo emergency or elective laparotomy. To achieve 90% power at the 5% significance level, 1006 patients will be required in each arm, which when allowing for losses to follow-up, 10% will be added to each arm, leaving the total projected sample size to be 2013 patients, who will be recruited across a 36-month enrolment period.

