### Power calculation

For planning purposes, it is assumed 15% of participants randomized to standard dressings will develop an SSI and the rate among patients receiving prophylactic, single-use NPWT will be 10% (that is a relative risk reduction of 33%, absolute risk reduction 5%). To achieve 90% power at the 5% significance level, a minimum of 1006 patients will be required in each arm. To allow for losses to follow-up and withdrawals, 10% will be added to each arm. Therefore, the total projected sample size for PROPEL-2 is 2013 patients. This power calculation for PROPEL-2 did not estimate or account for subgroups, including elective and emergency laparotomy wounds or surgical procedures performed.

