The primary focus will be to compare the two treatment groups on an intention-to-treat (ITT) basis, and this will be reflected in the analysis which will be reported together with appropriate diagnostic plots that check the underlying model assumptions. In addition to the ITT analyses, per-protocol (as treated) analyses will also be undertaken and reported in parallel to, but subsidiary to, the main analyses. Where possible the reasons for missing data will be determined. Although missing data is not expected to be a problem for this study, the nature and pattern of the ‘missingness’ will be considered—including in particular, whether data can be treated as missing at random (MAR). If judged appropriate, missing data will be imputed, using multiple imputation. The resulting imputed data sets will be analysed and reported, together with appropriate sensitivity analyses. Any imputation methods used for scores and other derived variables will be reviewed by the Data Monitoring Committee (DMC). Reasons for ineligibility, non-compliance, withdrawal or other protocol violations will be stated if available and any patterns summarized. More formal analysis, for example using logistic regression with ‘protocol violation’ as a response, may also be appropriate and aid interpretation.

All reported tests will be two-sided and considered to provide evidence for a significant difference if *P* values are less than 0.05 (5% significance level). A detailed statistical analysis plan (SAP) will be agreed with the DMC before commencement of the study. Any subsequent amendments to this initial SAP will be clearly stated and justified in the final report. Interim analyses of efficacy outcomes are not planned and will be performed only where requested by the DMC. Data will be analysed using Statistical Package for Social Sciences™ (SPSS™) version 26.0 (International Business Machines Corporation, Armonk, NY, USA).

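### Kaplan–Meier, if used as named to assess complication risk overall and by class, would modestly overstate that risk when deaths are censored; cumulative incidence curves fit the stated aim better

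*Protocol article*

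**What the plan says.** In the Statistical analysis section of the protocol article, temporal patterns of complications are to be shown graphically, and then "if appropriate a time-to-event analysis (Kaplan–Meier survival analysis) will be used to assess the overall risk and risk within individual classes of complications". Kaplan–Meier is the only time-to-event method named, and its stated target is risk, both overall and within each class.

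The sentence before it sets the main analysis of complications: "Other dichotomous outcome variables, such as complications related to the trial interventions, will be analysed in the same manner as the primary outcome". That means a mixed-effects logistic regression reported as odds ratios.

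Two other statements give the setting. The abstract describes adults "who are indicated to undergo emergency or elective laparotomy", and the internal pilot summary states: "Participating patients will have clinical follow-up for 6 months". The article does not say how a death during follow-up enters the time-to-event analysis, or whether death counts as a complication.

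**The concern.** A patient who dies without a wound complication can no longer have one. Kaplan–Meier with deaths censored treats that patient as still at risk and, in effect, gives them the later experience of the survivors. One minus Kaplan–Meier then estimates the risk in a hypothetical setting without death. The article asks for the risk itself, meaning the share of randomised patients who develop the complication by a given time. That share is always smaller if any deaths come first.

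At stake is the accuracy of the complication risks read off these curves, overall and by class. The point concerns a named method that does not match its stated target, not a detail left out of a condensed article.

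**Working it through.** The article gives no Kaplan–Meier estimate and no mortality figure, so there is nothing of its own to reproduce. The check asks how large the excess could be.

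**Inputs**
- Illustrative complication risks of 15% and 10%. These are the planning SSI rates for the two arms in the Power calculation section (for the control arm, "it is assumed 15% of participants randomized to standard dressings will develop an SSI"). They are borrowed only to give a realistic scale.
- Death risk d over the period of the curve, among patients without the complication: 5%, 10% and 15%. **This is an assumption.**
- Deaths censored, constant hazards, and no other source of bias. **These are also assumptions.**

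**Formulae**
- Complication hazard over the period: h1 = −ln(1 − KM), where KM is the risk read as one minus Kaplan–Meier.
- Death hazard over the period: h2 = −ln(1 − d).
- Cumulative incidence with death competing: CIF = h1/(h1 + h2) × [1 − exp(−(h1 + h2))].

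**Worked case: KM = 15%, d = 10%**
- h1 = −ln(0.85) = 0.1625 and h2 = −ln(0.90) = 0.1054, so the sum is 0.2679.
- 1 − exp(−0.2679) = 1 − 0.85 × 0.90 = 0.235.
- CIF = (0.1625/0.2679) × 0.235 = 0.1426, or 14.3%.

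**Range**

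| Assumed deaths | CIF when KM = 15% | Excess (points) | CIF when KM = 10% | Excess (points) |
|---|---|---|---|---|
| 5% | 14.63% | 0.37 | 9.75% | 0.25 |
| 10% | 14.26% | 0.74 | 9.50% | 0.50 |
| 15% | 13.88% | 1.12 | 9.24% | 0.76 |

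In relative terms the excess is about half the death risk. At KM = 15% it is 2.5%, 5.2% and 8.1%.

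**Sensitivity to the timing of deaths.** If every death came at the very start, one minus Kaplan–Meier would equal CIF/(1 − d). A Kaplan–Meier risk of 15% would then correspond to 15 × 0.95 = 14.25%, 15 × 0.90 = 13.5% or 15 × 0.85 = 12.75%. This is an extreme upper case. Deaths that come after most complications have already occurred would give less than the table shows.

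**Comparison with sampling error.** Taking the 1006 per arm stated in the Power calculation section, the standard error of a 15% risk is √(0.15 × 0.85/1006) = 0.0113, or about 1.1 points. Under constant hazards the excess is below one standard error at 5% and 10% deaths and about equal to it at 15%.

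**The case against.** The strongest reply is that little hangs on this sentence. The analysis is run only if judged appropriate, no test is attached to it, and the comparison of complications between arms is logistic. The article states no censoring rule, and event definitions and the handling of death commonly belong in the SAP, which is not shown. If death were itself counted as a complication, the overall curve would be free of the problem. The excess is also small against sampling error for plausible mortality.

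Most of this stands, and it sets the weight of the point. It does not remove it. The condition governs whether the analysis is done, not which method is used, and the only method named is Kaplan–Meier with risk as its target. Counting death as a complication would repair the overall curve but not the class-specific ones.

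A reader might infer more than the article supports:
- *That the trial's main result is overstated.* It is not. The SSI proportions at 30 and 90 days are compared by mixed-effects logistic regression, and the infection time pattern is touched only if SSI is among the complications plotted.
- *That the comparison between arms would be distorted.* The Kaplan–Meier sentence names no between-arm test, and nothing in the article suggests that mortality differs by dressing. With similar mortality, much of the excess would cancel.
- *That emergency patients would be worst affected.* No curves by urgency are planned. Urgency enters only as a fixed effect in the regression.
- *That class-specific curves failing to add up to the overall risk shows the fault.* Nothing makes the classes mutually exclusive, since one patient may have several complications. Cumulative incidence curves by class would not add up either.

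**Conclusion.** The point holds as a minor one. If the time-to-event analysis is done as named and deaths are censored, the reported complication risks will be modestly too high: by about 0.4 to 1.1 percentage points on a Kaplan–Meier risk of 15%, for assumed deaths of 5% to 15% under constant hazards. The direction is certain once any death precedes the event. The size rests wholly on the assumed mortality and its timing, because the article gives neither. The design, the sample size, the primary analysis and the logistic comparison of complications are not affected.

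**What to change.** In the Statistical analysis sentence, and in the SAP, replace Kaplan–Meier with cumulative incidence curves (Aalen–Johansen estimator) with death as a competing event. Present them by arm, for any complication and for each class, and tabulate deaths by arm alongside. State whether death counts as a complication. The curves can remain descriptive, because the planned logistic regression already provides the comparison.

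The cost is small. The date of death must be recorded for each patient who dies during follow-up, and the estimator may have to be run outside the SPSS version named in the article. No change to recruitment, visits or the primary analysis is needed.
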